## Abstract

**Background:**

Ischemic heart failure (IHF) has a poor prognosis in spite of optimal therapy. We have established a new allogeneic Cardiology Stem Cell Centre adipose-derived stromal cell (CSCC_ASC) product from healthy donors. It is produced without animal products, in closed bioreactor systems and cryopreserved as an off-the-shelf product ready to use.

**Study Design:**

A multicentre, double-blind, placebo-controlled phase II study with direct intramyocardial injections of allogeneic CSCC_ASC in patients with chronic IHF. A total of 81 patients will be randomised at 2 : 1 to CSCC_ASC or placebo. There is no HLA tissue type matching needed between the patients and the donors.

**Methods:**

The treatment will be delivered by direct injections into the myocardium. The primary endpoint is change in the left ventricle endsystolic volume at 6-month follow-up. Secondary endpoints are safety and changes in left ventricle ejection fraction, myocardial mass, stroke volume, and cardiac output. Other secondary endpoints are change in clinical symptoms, 6-minute walking test, and the quality of life after 6 and 12 months.

**Conclusion:**

The aim of the present study is to demonstrate safety and the regenerative efficacy of the allogeneic CSCC_ASC product from healthy donors in a double-blind, placebo-controlled, multicentre study in patients with IHF.

## 1. Background

Ischemic heart disease (IHD) caused by coronary artery disease is the most common cause of death with more than 17 million deaths worldwide each year and the major cause of hospital admissions [1]. It is an increasing economic health problem due to increasing morbidity in an ageing population. Conventional therapies have reduced the mortality of IHD significantly, but left an increasing number of patients with chronic IHD and/or ischemic heart failure (IHF) without further treatment options.

When looking for new treatment options, regenerative therapy with stem cells has been investigated intensively in several clinical studies in patients with acute or chronic IHD [2–4]. Several different cell populations have been investigated. Initially, it was mainly bone marrow-derived mononuclear cells (MNCs), mesenchymal stromal cells (MSCs), CD34^+^, CD133^+^, and endothelial progenitor cells. Later, cell populations have been isolated from the adipose tissue (adipose-derived mesenchymal stromal cells (ASCs)), placenta, umbilical cord, the heart, and several other tissues [2]. Presently, no consensus exists about the best cell type for clinical regenerative therapy.

The presence of MSC-like cells in all tissues of the body indicates their importance, and preclinical studies indicate that these cells have regenerative capacity regardless of tissue origin [4]. Most clinical studies have used BM-MSCs. However, from a feasibility point of view, ASCs are superior to BM-MSCs as a higher yield of ASCs can be isolated from abdominal adipose tissue compared to MSCs from the bone marrow. [5] Furthermore, ASCs grow faster than BM-MSCs during culture expansion [6].

We have conducted three clinical studies with autologous culture-expanded BM-MSCs and ASCs in patients with IHD with or without heart failure [7–11]. The treatments have been safe and the regenerative efficacy promising. The studies demonstrated improvements in left ventricular ejection fraction, heart tissue remodeling, exercise capacity, and relief of symptoms.

To implement and disseminate a new clinical therapy with stem cells to all potential candidates, safety and efficacy have to go hand in hand with feasibility; it has to be logistically easy to request and perform the treatment. However, there are many logistical obstacles in the presently used clinical models for autologous MSC therapies within cardiology: Invasive harvesting of bone marrow or aspiration of abdominal adipose tissue in all patients was followed by several weeks of culture expansion with a huge variation in proliferation rate and cell yield from patient to patient. This makes it difficult to treat patients with a standardised number of cells in clinical studies. Moreover, it is logistically difficult to schedule the treatment procedure due to large variations in cell production time.

Additionally, the number of cells delivered to the patient may be of importance for the treatment efficacy and the patients may need more than one treatment session to get relief from cardiac symptoms.

We have tackled these serious hurdles by establishing new ASC cultivation protocols with human platelet lysate in closed bioreactor systems and by establishing a centralised production of an allogeneic Cardiology Stem Cell Centre adipose-derived stromal cell (CSCC_ASC) product from healthy donors, which can be stored in nitrogen vapour containers as an off-the-shelf product in the hospital ready to be used without any delay.

This newly developed cryopreserved product, CSCC_ASC, from healthy donors was safe and feasible in a phase I study in patients with IHF [12]. In addition, we observed a tendency towards efficacy in patients although the study was not powered for that.

This study was established to investigate both the safety and the efficacy with regard to the regenerative potential of this newly developed CSCC_ASC product. The present report will outline the rationale and design of this multicentre, double-blinded, placebo-controlled phase II study using intramyocardial delivered allogeneic CSCC_ASC in patients with IHF.

## 2. Methods

### 2.1. Study Design and Population

The study protocol complies with the Declaration of Helsinki and was approved by the Danish National Committee on Health Research Ethics (number 1717872) and Danish Medicines Agency (EudratCT number 2015-001560-19). The study is registered with clinicalTrials.gov (NCT02387723). The local Good Clinical Practice Unit from the capital region of Denmark will monitor the study.

The study will include 81 patients with IHF between 30 and 85 years of age with reduced left ventricular ejection fraction (LVEF) (≤45%) evaluated by echocardiography, New York Heart Association (NYHA) classes II-III, no further revascularization options and on maximal tolerable heart failure medication. Inclusion and exclusion criteria are described more in detail in Table 1.

The patients will be screened and followed locally in the four participating clinical cardiology sites. All patients will be treated centrally at the Department of Cardiology, Rigshospitalet University Hospital Copenhagen in a 2 : 1 randomisation with either CSCC_ASC or placebo (isotonic saline).

Patients will have follow-up visits 1, 3, 6, and 12 months after treatment for safety and efficacy evaluation (Figure 1 and Table 2).

### 2.2. Cell Production

The investigational cell product, CSCC_ASC, will be produced in the Cardiology Stem Cell Centre, Rigshospitalet University Hospital Copenhagen in an approved good manufacturing practice (GMP) facility following the description in an approved Investigational Medicinal Product Dossier.

The cell product will derive from 5 to 7 healthy donors. The donor eligibility will be determined by a donor interview, a questionnaire, and testing for infectious disease markers including human immunodeficiency virus (HIV) and human T-cell lymphotropic virus (HTLV) types I/II by serum analyses within 30 days prior to liposuction. In addition, a blood sample will be drawn on the day of donation for repeated serology and nucleic acid testing of HIV and hepatitis B and C.

The donors will have an abdominal liposuction (100–150 mL of lipoaspirate). The preparation of lipoaspirates, isolation of stromal vascular fractions, and expansion of adipose-derived stromal cells in Quantum Cell Expansion Systems (Terumo, US) will be performed as previously described [12–14]. Each CSCC_ASC treatment vial will consist of ASCs from one donor only.

The production unit will produce and deliver both the CSCC_ASC and the placebo (isotonic saline) batches based on the randomisation code. It will label the Investigational Medicinal Product (IMP) and placebo in accordance with the legislation and keep the randomisation code until finalization of the clinical trial. The final cell products will be stored in nitrogen vapour containers until clinical use.

### 2.3. Cell Treatment

There will be no humane leucocyte antigen (HLA) tissue type matching between the donor and the patients. The IMP will be thawed and prepared for injection immediately before treatment. The treatment ampoules are transparent, and the colour of the placebo product is slightly different from that of the cell product. Therefore, to assure the blinding of the treatment, the clinical teams which are responsible for the screening and follow-up of the patients will not participate in the treatment procedure or be in the catheterization laboratory during the treatment. The staff in the catheterization laboratory will be instructed to avoid comments on the delivered product.

### 2.4. NOGA-Guided Injection

A 3D map of the left ventricle will be created using the NOGA XP® system (Biological Delivery System, Cordis, Johnson & Johnson, USA) [7–10]. With the MYOSTAR® injection catheter (Biological Delivery System, Cordis, Johnson & Johnson, USA), the IMP (100 million CSCC_ASCs or placebo) will be delivered into the myocardium by 12–20 injections of 0.3–0.4 mL. The injections will be performed in the viable myocardial tissue with a unipolar voltage > 6 mV. Plasma CKMB and Troponin will be measured before, immediately after, 6 hours and at day 1 after the injections in order to assess possible myocardial effects.

### 2.5. ECHO and CT Scans

Patients will undergo cardiac computed tomography (CT) and echocardiography (ECHO) scans with contrast at baseline and six months after treatment [8]. For cardiac CT (320 slice, Aquilion, Toshiba, Tokyo, Japan, or Flash dual source, Siemens, Siemens Healthcare GmbH, Germany), the R-R interval and multisegmental image reconstruction will be performed with the most recent scanner software. ECHO will use parasternal and apical two 2D and 3D views. CT scans with contrast will not be performed if plasma creatinine > 130 *μ*mol/L or in patients with known contrast allergy.

All image data will be stored in a central server and be analysed blinded. CT scans will be analysed with the cvi42 postprocessing tool (Circle Cardiovascular Imaging, Calgary, Alberta, Canada). Endocardial and epicardial borders will be traced manually in end-diastole and end-systole starting from the mitral plane and ending at apex. ECHO will be analysed using IntelliSpace Cardiovascular (Philips Medical Systems, Best, the Netherlands) to obtain conventional as well as deformation and 3D volumetric measures.

### 2.6. Biomarkers and Alloantibodies

All donors will have an intermediate resolution typing of human leucocyte antigen- (HLA-) A, HLA-B, HLA-C, DRB1, DRB345, DQA1, DQB1, DPA1, and DPB1 loci by real-time PCR with subsequent melting point analyses using a Linkseq 384-well complete typing kit (Linkage Biosciences Inc., CA, US). Patient blood samples are drawn at baseline and follow-up and will be stored for later centralized analyses of biomarkers and the presence of alloantibodies with the LABScreen HLA classes I and II single antigen bead assay on a Luminex 100 (One Lambda Inc., Thermo Fischer, Canoga/Los Angeles, CA, USA).

### 2.7. Endpoints

The *primary endpoint* is the difference between the two groups of the change in left ventricle end-systolic volume (LVESV) from baseline to 6-month follow-up measured with CT scans and with ECHO scans in patients with reduced kidney function.

The *secondary endpoints* are safely evaluated by the development of alloantibodies and laboratory safety measurements, incidence and severity of serious adverse events, and suspected unrelated serious adverse events 1, 3, 6, and 12 months after treatment. Other endpoints are changes in LVEF, left ventricle end-diastolic volume (LVEDV), stroke volume, cardiac output, and end-diastolic myocardial mass at 6-month follow-up. The changes in left ventricle function will be measured by CT and ECHO.

Other secondary endpoints are changes in NYHA and CCS class, Kansas City Cardiomyopathy Questionnaire (KCCQ), Seattle Angina Questionnaire, EQ5D3L Questionnaire, 6-minute walking test, and NT-pro-BNP.

We will also asses changes in the following endpoints alone and combined:

(1) Death, hospitalization for worsening heart failure including implanting of a biventricular pacemaker, and hospitalization because of ventricular tachycardia or fibrillation 1, 2, and 3 years after treatment.

(2) Death, hospitalization for any cardiovascular reason, hospitalization for worsening heart failure including inserting of a biventricular pacemaker, and hospitalization because of ventricular tachycardia or fibrillation 1, 2, and 3 years after treatment.

### 2.8. Power Calculation

#### 2.8.1. Definition and Justification (Power Calculation) of Sample Size

The enrolment of 81 patients in a 2 : 1 randomisation (54 : 27) will have a statistical power above 90% for the detection of an absolute change between groups in LVESV of 10 mL expected SD of 13 mL and 11.6 mL with expected SD of 15 mL. For all, alpha values of 5% were used. Change between groups in LVEF of 3.1% with expected SD of 4% and 3.9% with expected SD of 5% will also have statistical power above 90% with a 5% alpha value.

Power calculations are based on our recently finalized double-blind, placebo-controlled trial with 60 patients with IHF (MSC-HF trial); we compared direct intramyocardial injections of autologous MSCs or placebo in a 2 : 1 randomisation design. The six-month follow-up demonstrated significant improvement in LVESV with a difference between groups of 13.0 ± 12.9 mL (*p* = 0.001). There were also significant improvements in LVEF with a difference of 6.2 ± 3.8% (*p* < 0.0001) between MSC and placebo-treated patients.

In the MSC-HF trial, cardiac measurements were done by magnetic resonance imaging (MRI) and CT. Since the SD is often a little higher for echocardiographic measured parameters compared to the data obtained using MRI and CT, we used slightly higher SD in our power calculations.

#### 2.8.2. Safety and Ethical Considerations

The Cardiology Stem Cell Centre has conducted several clinical studies with direct injection of stem cells or genes into the myocardium with the methodology employed without any safety issues raised [7–10].

The newly developed CSCC_ASC product has been evaluated in 10 patients with IHF without any safety concerns [12]. Each patient was treated with cells from one of three donors, and no matching between the donor and the patient tissue types was performed. There were no procedure-related complications to the direct intramyocardial injection of CSCC_ASC. During the 6-month follow-up period, four out of ten patients developed donor-specific de novo HLA class I antibodies and two other patients had prior to the treatment donor-specific antibodies. None of the patients had any clinical symptoms, changes in biochemical parameters, or inflammatory signs indicating an immunization.

Based on these data and the safety data from other groups using allogeneic MSC therapy in patients, we consider it safe to continue with the present clinical phase II trial.

During the two CT scans, patients may receive a radiation dose of up to 20 mSv depending on body weight, heart rate, and regularity of the heart rate during the scan. It can be calculated that the lifetime risk of dying from cancer hereby theoretically increases by 0.1%. The patients receiving a maximum radiation dose of 20 mSv will have their lifetime risk of dying from cancer increased from 25% to 25.1%. The above estimation is based on calculations done by the National Institute of Radiation Protection, Denmark.

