(10) History with malignant disease within five years of inclusion or suspected malignancy, except treated skin cancer other than melanoma
(11) Pregnancy or lactation
(12) Other experimental treatment within four weeks of baseline tests
(13) Participation in another intervention trial
(14) Known hypersensitivity to dimethyl sulfoxide (DMSO)

**Table 2 tab2:** MSC-HF II study: summary of events.

Event	Screening/baseline	D1	D2	D3	M1	M3	M6	M12
Informed consent	X							
History/physical	X	X		X	X	X	X	X
NYHA	X	X			X	X	X	X
CCS	X	X			X	X	X	X
ECG	X	X		X	X	X	X	X
Biochemistry local laboratory	X	X	X	X	X	X	X	X
Biomarkers	X	X			X	X	X	X
HLA tissue typing	X							
HLA tissue antibodies	X				X	X	X	X
6-minute walking test	X					X	X	X
Chest X-ray	X							
CCT	X						X	X
KCCQ	X					X	X	X
SAQ	X					X	X	X
EQ5D3L	X					X	X	X
NOGA mapping			X					
IMP injection			X					
Echocardiography	X		X				X	
Holter monitoring	X	X	X	X				
AE evaluation			X	X	X	X	X	X

D: day; M: month; AE: adverse events; CCS: Canadian Cardiovascular Society functional classification; CCT: cardiac computed tomography imaging; ECG: electrocardiogram; HLA: humane leucocyte antigen; IMP: investigational medicinal product; KCCQ: Kansas City Cardiomyopathy Questionnaire; NYHA: New York Heart Association functional classification; SAQ: Seattle Angina Questionnaire. EQ5D3L questionnaire.

**Table 3 tab3:** Mesenchymal stromal cell trials in patients with acute myocardial infarction.

Reference	Number of patients	Cell type	Design	Delivery route	Endpoints
*Allogeneic*					
Hare et al. 2009 [17]	53	MSC	RPCT	IV	Safe. Improved FEV1
*Autologous*					
Chen et al. 2004 [18]	69	MSC	RPCT	IC	Improved LVEF, LVESV, perfusion
Katritsis et al. 2007 [19]	22	MSC	Open	IC	Improved wall motion and perfusion
Yang et al. 2010 [20]	16	MSC	Open	IC	Safe and feasible. No clinical improvement
Houtgraaf et al. 2012 [21]	14	MSC	RPCT	IC	Improved perfusion and reduced scar tissue

FEV1: forced expiratory volume in 1 second; IC: intracoronary; IV: intravenous; LV: left ventricular; LVEF: left ventricular ejection fraction; RPCT: randomised placebo controlled trial.

**Table 4 tab4:** Mesenchymal stem cell trials in patients with chronic ischemic heart disease.

Reference	Number of patients	Cell type	Design	Delivery route	Endpoints
*Allogeneic*					
Hare et al. 2012 [22]	30	MSC	RO	IM	Safety and feasible
Perin et al. 2015 [23]	60	MSC	RSCT	IM	Safety and feasible
Kastrup et al. 2017 [12]	10	ASC	Open	IM	Safety and feasible

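### Sections 2.5 and 2.8.2 count two cardiac CT scans, but Table 2 schedules three, and the stated radiation maximum covers only two

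*Protocol article*

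**What the plan says.** Section 2.5 sets the imaging times: "Patients will undergo cardiac computed tomography (CT) and echocardiography (ECHO) scans with contrast at baseline and six months after treatment". For CT, that is two scans.

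Section 2.8.2 uses the same count for the exposure statement: "During the two CT scans, patients may receive a radiation dose of up to" 20 mSv. For patients at that maximum it gives a "lifetime risk of dying from cancer increased from 25% to 25.1"%.

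Table 2, the visit schedule, has a row for CCT, which its footnote defines as cardiac computed tomography. The row is marked at screening/baseline, M6 and M12, which makes three scans.

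Section 2.7 defines the primary endpoint as the between-group difference in change in "left ventricle end-systolic volume (LVESV) from baseline to 6-month follow-up measured with CT scans", with echocardiography for patients with reduced kidney function. The other ventricular measures, ending with "stroke volume, cardiac output, and end-diastolic myocardial mass at 6-month follow-up", have the same time point.

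The abstract gives 12-month assessment only for non-imaging outcomes: "Other secondary endpoints are change in clinical symptoms, 6-minute walking test, and the quality of life after 6 and 12 months".

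**The concern.** The two counts cannot both be right. Either the schedule orders a CT that no stated endpoint needs, or the dose and cancer risk presented as the maximum leave out one scheduled scan of three.

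This matters for participants more than for inference. Table 2 is the only visit-by-visit schedule in the article, and patients are followed locally at four sites. A site that follows the table would perform a third contrast CT. Section 2.5 already withholds contrast CT when plasma creatinine exceeds 130 μmol/L or there is a known contrast allergy, so the protocol itself treats contrast exposure as something to limit.

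**Working it through.** **1. Is the third mark an artefact of reading the table?** The Table 2 header has nine fields: the event name and eight time points. The CCT row also has nine, with marks under screening/baseline, M6 and M12. Neighbouring rows line up sensibly: the 6-minute walking test falls at baseline, M3, M6 and M12, and echocardiography at baseline, D2 and M6. A shifted row could move a mark but could not turn two marks into three.

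**2. The sources side by side**

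| Place | CT time points given or implied | Count |
|---|---|---|
| Section 2.5 | baseline, 6 months | 2 |
| Section 2.7, imaging endpoints | baseline, 6 months | 2 |
| Section 2.8.2 | count stated, times not given | 2 |
| Table 2, CCT row | baseline, M6, M12 | 3 |

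**3. Does any 12-month outcome need CT?** The outcomes with a time point of 12 months or later are safety, symptoms, walking test, quality of life and clinical events. None is measured by CT. Echocardiography, the substitute for patients with reduced kidney function, has no M12 mark, so a 12-month CT volume would have no counterpart in those patients.

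**4. The plan's own figure.** Inputs from Section 2.8.2: two scans, maximum 20 mSv in total, added risk 0.1 percentage points, starting risk 25%.
- 25% + 0.1 = 25.1%. The stated figure is correct for two scans.

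**5. The figure if the M12 scan is performed.** Two assumptions are needed: the same maximum dose for each scan, and risk proportional to dose.
- Dose per scan: 20 / 2 = 10 mSv
- Three scans: 3 × 10 = 30 mSv
- Risk per mSv: 0.1 / 20 = 0.005 points
- Three scans: 30 × 0.005 = 0.15 points, so 25% becomes 25.15%
- Third scan alone: 10 × 0.005 = 0.05 points
- Relative to the stated maximum: 30 / 20 = 1.5, so dose and added risk are both 50% higher

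**6. Range if the stated 0.1 is a rounded value (0.05 to 0.15).**
- Three scans: 1.5 × 0.05 = 0.075 to 1.5 × 0.15 = 0.225 points
- Third scan alone: 0.5 × 0.05 = 0.025 to 0.5 × 0.15 = 0.075 points

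**The case against.** The strongest reply is that the text need not be a complete list of imaging. Table 2 also marks echocardiography on D2, which Section 2.5 does not mention, so absence from Section 2.5 does not by itself show that the M12 CT is a slip. Section 2.1 says the visits through 12 months serve both safety and efficacy, which would be compatible with exploratory 12-month imaging described in the full protocol. On that view, deleting the mark outright could make the article wrong and leave the exposure understated. The effect is also small, not every patient is eligible for contrast CT, and no analysis changes.

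Much of this stands. The article does not prove which side is wrong, and the absolute risk is small. But the objection does not remove the conflict. Section 2.8.2 does more than omit a scan: it counts two. A general sentence about the purpose of the visits names no imaging and cannot reconcile that count with three marks. If 12-month imaging is planned in the full protocol, then the exposure statement is what needs correcting.

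It is also fair that 30 mSv is an extrapolation. Section 2.8.2 says the dose depends on body weight, heart rate and regularity of rhythm, so the figure illustrates the size and is not a dosimetry result.

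**Conclusion.** The contradiction is real: two CT scans in Sections 2.5 and 2.8.2, three in Table 2. The balance of the article, above all the explicit count in Section 2.8.2 and the six-month timing of every ventricular imaging endpoint, points to an error in one table cell. In that case 20 mSv and 25.1% stand.

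If the third scan is intended, the stated maximum is too low by about 10 mSv and 0.05 percentage points (0.025 to 0.075 allowing for rounding), under the equal-dose and linear-risk assumptions. Confidence in the mismatch is high; confidence in which side is the slip is lower. The point should be fixed because it decides whether patients receive an extra scan and whether the stated risk is complete. It has no bearing on power, sample size or the primary analysis.

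**What to change.** Check the CT schedule against the approved full protocol. Unless a 12-month CT is planned there, delete the M12 mark from the CCT row of Table 2. This costs one table cell.

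If the scan is intended, add a sentence in Section 2.5 giving the third time point and a sentence in Section 2.7 stating which outcome it serves. Then restate the exposure in Section 2.8.2 for three scans. About 30 mSv and 0.15 percentage points is the size to expect under the assumptions above, but the published figure should come from the radiation protection source used for the current estimate.
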